### Study Procedure

Figure 1 shows the study flow and Table 1 shows the study time schedule. The study will include run-in period, random enrollment, and treatment period. The run-in period was 1 month, and treatment period is at least 2 years. All the subjects will receive oral and written information regarding the study. Written informed consent will be obtained by the doctors involved in the trial.

**Table 1 T1:** Study flow chart.

**Research phase**	**Run-in**	**Random enrollment**	**Treatment period**													
Time	−1 Month	−7–0 days	1 M ± 7days	2 M ± 7	3 M ± 7	4 M ± 7	5M ± 7	6 M ± 7	7 M ± 7	8 M ± 7	9 M ± 7	10 M ± 7	11 M ± 7	12 M ± 7	Until the 48th month^#^	When an end event occurs
**Basic Information**																
Informed consent form	•															
General information and medical history		•														
Vital signs	•	•	•	•	•	•	•	•	•	•	•	•	•	•	•	•
**Treatment**																
Inclusion/exclusion criteria	•	•														
Assign random number		•														
Distributing research drugs		•			•			•			•			•	※	
Record combined medication		•			•			•			•			•	※	•
Drug recovery					•			•			•			•	※	•
**Safety indicators**																
Blood/urine routine		•						•						•	※	•
Liver and kidney function		•						•						•	※	•
12-lead ECG		•						•						•	※	•
Serum NO, E-1		•												•	※	•
Thyroid function		•														
NYHA classification		•														
Adverse event assessment	•	•	•	•	•	•	•	•	•	•	•	•	•	•	•	•
**Efficacy index**																
Fasting blood glucose (capillary)	•	•	•	•		•	•		•	•		•	•		※	
Two hours post-prandial blood glucose (capillary)	•	•	•	•		•	•		•	•		•	•		※	
OGTT test		•	⊚	⊚	•	⊚	⊚	•	⊚	⊚	•	⊚	⊚	•	※	•
Four blood lipids		•						•						•	※	•
Weight, BMI, waist circumference	•	•	•	•	•	•	•	•	•	•	•	•	•	•	•	•
Fasting insulin		•						•						•	※	•
Glycated hemoglobin		•						•						•	※	•
C-reactive protein		•						•						•	※	•
Urinary microalbumin		•						•						•	※	•
Carotid ultrasound		•												•	※	•
Brachial index		•												•	※	•

# *13th−48th month of follow-up, please continue the first 12 months of the visit; ⊚: If the blood glucose measured by the capillaries is diagnosed as diabetes, please perform the OGTT test. ※: Please check the 1st−12th months of follow-up at the end of the 13th to 48th month. •: Items to be performed during follow-up*.

### Screening Cycles

Subjects who are diagnosed with impaired glucose tolerance syndrome will be given a 1-month general lifestyle intervention.

This visit should include the following:

Signing informed consent;Physical examination;Detection of fasting blood glucose and 2-h postprandial blood glucose by capillaries;Guidance for subjects on general lifestyle interventions.

### Intervention Cycles

Eligible subjects will be randomly assigned to receive general lifestyle intervention + Jinlida granules at a dose of 9 g or general lifestyle intervention + placebo, orally, three times daily. The run-in period is 1 month, and the intervention will last 24–48 months. Follow-up will last 24 months.

### Outcome Measure

#### Primary Outcomes

Incidence of type 2 diabetes.

#### Secondary Outcomes

Changes in the number of components of the metabolic syndrome;Changes in single indicators (waist circumference, blood pressure, TG, HDL-C) in metabolic syndrome;Carotid intima-media thickness (IMT);Fasting insulin;Ankle brachial index;Glycated hemoglobin (HbA1c);Endothelial function test: Serum NO, ET-1;C-reactive protein;Urinary microalbumin to creatinine ratio (ACR).

### Sample Size Calculation

According to “Lian et al. (23),” after 1 year of follow-up, the average annual incidence of diabetes in the placebo group was 29.32%. “Gao et al. (24)” demonstrated a cumulative incidence of diabetes in placebo group after 3 years of follow-up was 43.86%.

Our hypothesis assumes that the incidence of diabetes in the control group would be 40.0% after 2 years of intervention and the HR would be expected to be 0.75—the study drug is predicted to reduce the risk by 25%—employing α = 0.05, β = 0.20. The study group and the control group will be allocated in a 1:1 ratio. The study period will last 4 years, including 2 years of medication treatment and 2 years of follow-up. PASS16 software will be employed to calculate the sample size, each group should contain 395 subjects. Considering a 10% the violation rate and issues of inter-center case allocation, a total of 880 cases and evaluation of number of endpoint events 209:171 will be required to reach statistical significance.

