## Abstract

**Background:** Metabolic syndrome (MS) is a powerful risk factor for cardiovascular and cerebrovascular diseases. Although lifestyle intervention reduces several of the symptoms of the syndrome and cardiovascular risks, the lifestyle intervention that yields the benefits is restrictive. Jinlida is a Chinese patent medicine that has shown activity in type 2 diabetes, which has been approved in China. Preclinical studies in Jinlida granules support an improved role of abnormal glucose and lipids metabolism as well as reducing weight. Here, we describe the protocol of an ongoing clinical trial investigating a new therapy for metabolic syndrome in patients with abnormal glucose metabolism.

**Methods:** This study will enroll 880 subjects (aged 18–70 years) who have metabolic syndromes with abnormal glucose metabolism. All the participants in a double-blind, parallel, randomized, placebo-controlled trial, will receive Jinlida or placebo, orally, 9 g/time, three times daily for 2–4 years period on the basis of lifestyle intervention. The primary outcome measure (Incidence of type 2 diabetes) will be assessed during intervention cycles. Adverse events were monitored. All statistical tests will be performed using a two-sided test, and a *p* ≤ 0.05 (two-sided test) will be considered to be statistically significant results.

**Discussion:** Results from this study will provide evidence on whether incorporating oral Jinlida granules treatment into lifestyle intervention can delay or inhibit the development of diabetes mellitus in metabolic syndrome subjects with abnormal glucose metabolism.

**Clinical trial registration:** Registered at http://www.chictr.org.cn/enIndex.aspx. Trial registration number: ChiCTR1900023241.

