### Intervention

#### Treatment

Study group: general lifestyle intervention + Jinlida granules (three times a day at a dosage of 6 g each time) drug consumed with boiled warm water;

Control group: general lifestyle intervention + placebo (three times a day at a dosage of 6 g each time); drug consumed with boiled warm water;

The research drugs are recommended to taken after meals. If the patient has an intolerable adverse event that considered as relevant to the study drug based on the investigator's consideration, the patient should discontinue the medication. Treatment duration is at least 2 years.

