#### Statistical Analysis Method

□ All statistical tests will be performed using a two-sided test, and a *p* <0.05 (two-sided test) will be considered to be statistically significant results (except for special instructions).□ Descriptive analysis: This data is described by the number of cases and the composition ratio. The measurement data are described by means of mean, standard deviation, maximum value, and minimum value. The non-normal distribution data are described by median, 25th and 75th quantiles. A comparison between the two groups of general conditions will be based on outcomes. Quantitative data will be compared between groups using group *t*-test or Wilcoxon rank sum test, classification data using chi-square test, or exact probability method, grade data used Wilcoxon rank sum test, or CMH test, as appropriate.

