### Current Status

Patients started enrolling in this trial on August 2019. As of May 2020, 182 patients were screened and 65 identified as candidates signed the informed consent. Currently, there is no subject completing the study. Relevant protocol modifications will be registered at http://www.chictr.org.cn. Trial registration number: ChiCTR1900023241

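### The sample size section describes a treatment and follow-up schedule that its own event count was not computed from, and the protocol's durations do not agree

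*Protocol article*

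**What the plan says.** All of the following is from the protocol article.

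- Sample Size Calculation assumes 40.0% diabetes incidence in the control group after two years, a hazard ratio of 0.75, 1:1 allocation, and error rates given as "employing α = 0.05, β = 0.20". It arrives at 395 per group and describes the duration thus: "The study period will last 4 years, including 2 years of medication treatment and 2 years of follow-up". After a 10% allowance it concludes that "a total of 880 cases and evaluation of number of endpoint events 209:171 will be required to reach statistical significance".
- Statistical Analysis Method: "All statistical tests will be performed using a two-sided test".
- Study objectives, and Setting and Participants: enrolment takes two years.
- Abstract: treatment runs two to four years, and the primary outcome "will be assessed during intervention cycles".
- Treatment: "Treatment duration is at least 2 years". Study Procedure gives the same minimum.
- Intervention Cycles: 24 to 48 months of intervention, and then "Follow-up will last 24 months".
- Table 1: the treatment period extends to month 48. Its footnote calls months 13 to 48 follow-up and repeats the first-year visits.
- Primary Outcomes: incidence of type 2 diabetes, with no time point.

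**The concern.** The power of a time-to-event comparison rests on how many events accrue and on the hazard ratio over the period in which they accrue. Both depend on how long subjects are treated, how long they are observed, and whether events after the end of treatment count. The sentence that justifies the sample size splits four years into a medication phase and a follow-up phase. It mentions neither the accrual period nor a common close. The other sections give durations that differ from it and from one another. If the 24-month follow-up in Intervention Cycles comes after the 24 to 48 months of intervention, each subject would be in the study for 48 to 72 months, which does not fit a four-year study with two years of enrolment.

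A reader therefore cannot tell which design the 80% power belongs to. The last sentence adds a second problem: it turns an expected event split into a condition for significance and attaches it to the wrong number of subjects.

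**Working it through.** **Inputs.** Control incidence 40.0% at two years, hazard ratio 0.75, 395 per arm, 10% allowance, α = 0.05 and β = 0.20 (Sample Size Calculation); two-sided tests (Statistical Analysis Method); two-year enrolment (Study objectives). Exponential event times are assumed.

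**Step 1: hazards.** Control: −ln(0.6)/2 = 0.2554 per year. Jinlida: 0.75 × 0.2554 = 0.1916 per year.

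**Step 2: events required.** Schoenfeld: 4 × (1.960 + 0.842)² / (ln 0.75)² = 4 × 7.849 / 0.0828, which gives 380 events. The protocol's 209 + 171 is also 380.

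**Step 3: reproduce the stated figures.** With uniform accrual over two years and a common close at year 4, observation is uniform on two to four years, and

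P(event) = 1 − (e^(−2λ) − e^(−4λ)) / (2λ).

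- Control: 1 − (0.6000 − 0.3600)/0.5108 = 0.5302; × 395 = 209.4.
- Jinlida: 1 − (0.6817 − 0.4648)/0.3831 = 0.4337; × 395 = 171.3.
- Power: Φ(√(380.7/4) × 0.2877 − 1.960) = Φ(0.847) = 80.1%.
- Size: 380/(0.5302 + 0.4337) = 394.3, so 395 per arm; 790/0.9 = 878, rounded to 880.

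Every stated figure is recovered. Another design does the same: a fixed observation of about 2.96 years per subject at a constant hazard ratio of 0.75 gives 209.3 and 170.8 events.

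**Step 4: power under the other readings, 395 per arm.** Rows with a constant hazard ratio use the Step 3 power formula. Rows in which the ratio changes at two years use a log-rank non-centrality integrated over time, with power Φ(|z| − 1.960).

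| Reading | Events, control : Jinlida | Power |
|---|---|---|
| Two treated years only | 158 : 126 (284) | 67.8% |
| Treatment stops at 2 years, all observed 4 years, HR 1.0 after stopping | 253 : 233 | 45.5% (z = 1.846) |
| Same, common close at year 4 | 209 : 184 | 53.6% (z = 2.051) |
| HR 0.875 after stopping, all observed 4 years | 253 : 223 | 68.9% |
| Same, common close at year 4 | 209 : 178 | 67.7% |
| HR 0.75 throughout, common close at year 4 | 209 : 171 | 80.1% |
| HR 0.75 throughout, all observed 4 years | 253 : 211 (464) | 87.3% |

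First row: 395 × 0.40 = 158.0 and 395 × (1 − 0.6817) = 125.7. The post-treatment hazard ratios of 1.0 and 0.875 are assumptions made here to show the range; the protocol gives none.

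With 440 per arm and no losses, the figures are 72.5% for the first row, 49.5% and 58.1% for the two rows with no effect after stopping, and 90.5% for the last row.

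**Step 5: the closing sentence.** With 380 events the critical hazard ratio is exp(−1.960 × 2/√380) = exp(−0.201) = 0.818, so significance does not require the split expected at 0.75. As a rough check on crude proportions of 395 per arm, 204 : 176 gives z = 0.0709/0.0356 = 1.99, p = 0.046, whereas 209 : 171 gives z = 0.0962/0.0356 = 2.71, p = 0.007. The split also belongs to 790 subjects: 880 with full data would be expected to give 440 × 0.5302 = 233 and 440 × 0.4337 = 191.

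**The case against.** The strongest defence is that the calculation is right and only its description slipped. In this protocol follow-up does not clearly mean off treatment. The Blinding section has drug dispensed during the follow-up period, and the Table 1 footnote uses the same word for months 13 to 48, which repeat visits that include drug distribution. Two to four years, at least two years, and 24 to 48 months are all compatible with a common close after two years of accrual. On that view the sample size sentence may be a mislabelled two years of accrual plus two years of minimum follow-up, with no power lost. This is plausible and it limits the finding. It does not remove it: the sentence as printed says something else, the separate 24-month follow-up in Intervention Cycles remains unexplained, and the document does not settle the matter.

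A reader might infer that the trial as described has only 45–68% power. The documents do not support that. The upper end ignores the two years of follow-up that the sentence includes, and the lower end needs the effect to vanish when treatment stops, which is stated nowhere. The same wording with a persisting effect gives 80–87%.

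A reader might also infer that 209 : 171 can arise under one schedule only, which Step 3 disproves, or that blinded staff must count events by arm, which no section asks. Projecting a recruitment shortfall from the early enrolment snapshot would be a straight-line extrapolation and is a separate matter. Closing the trial on an event count would be a design preference, not the correction of an error.

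**Conclusion.** The point stands as a contradiction in the basis for the stated power, not as an error in the sample size. The figures match two to four years of observation per subject with a constant hazard ratio of 0.75. The sentence presented as their basis describes a different division of the four years and conflicts with the Abstract, Treatment, Study Procedure, Intervention Cycles and Table 1.

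Depending on the reading, power at 395 per arm lies anywhere from about 45% to 87%. These values rest on exponential event times and the protocol's own incidence and hazard ratio. The values below 60% also rest on the unstated assumption of no effect after stopping. The Abstract's link between the primary outcome and the intervention cycles suggests that only events during treatment count; if treatment were also two years, the figure would be about 68%.

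Independently of the schedule, the closing sentence is wrong: it presents an expectation at a hazard ratio of 0.75 from 790 evaluable subjects as a count needed for significance among 880.

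**What to change.** 1. Reconcile the Abstract, Treatment, Study Procedure, Intervention Cycles, Sample Size Calculation and Table 1 to one treatment and follow-up schedule. Which schedule is the sponsor's decision.
2. In Sample Size Calculation, state the accrual period, the observation window per subject, and whether diabetes diagnosed after treatment ends counts towards the primary outcome.
3. Restate expected events and power for that schedule. If events after treatment count, state the hazard ratio assumed for that period.
4. Replace the closing sentence. If the programmed design is the one intended, this would do: about 380 events in total, expected from 395 evaluable subjects per arm, give 80% power to detect a hazard ratio of 0.75 at a two-sided significance level of 0.05; 880 subjects are enrolled to allow for a 10% violation rate.

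The cost is protocol wording and one rerun of the power calculation. The downside is a less favourable stated power if a shorter treated or observed period is what is meant.

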### Randomization

Subjects who sign an informed consent form will receive a screening number consisting of two parts. The first two digits are the center number, and the last three digits are sequentially added according to the order in which the subjects are screened. Subjects will be randomized using a central randomized system. When the subjects meet the enrollment criteria, the clinical study coordinator will be required to enter the subject's general information (name, age, gender) into an interactive voice/network response system (IWRS/IVRS). There they will obtain a random number and a drug number for a corresponding visit. Drugs will be distributed randomized subjects according to the drug number.

### Blinding

The drug packaging shall be prepared by the blinding personnel of the statistical unit which is the unrelated the trial. According to the drug packaging number generated by the software and the corresponding intervention group, the drug packaging number of the research drug and the control drug shall be filled in (or pasted on) the label. The second-level blind bottom will be produced during on-the-spot blinding, which is reserved in sponsor unit.

This trial will use a central randomized system to dispense medications during the follow-up period, so the medications are packaged at follow-up intervals. The random number assigned to each subject will be unique, except that the package number of the drug received during different follow-up period will differ, but the corresponding treatment plan will remain consistent. All blinded personnel must sign the blinding record and make a document for the clinical trial. The drug package number and confirmation code information will be imported into the DAS for IWRS system after blinding, and are used when applying for random numbers, dispensing drugs, and unblinding online.

### Data Collection and Management

The investigator should ensure that the data is correctly, completely, clearly, and timely entered into the case report form based on the original observations of the subject. The auditor shall monitor whether the research is conducted in accordance with the research plan and confirm that whether all case report forms are completed correctly and consistent with the original data. If errors and omissions are made, the researcher shall be promptly corrected. The case report form after the inspection by the auditor needs to be transmitted to the data administrator of the clinical research in time. The data administrator should compile the data entry-program for data management. In order to ensure the accuracy of the data, two data entry personnel should independently perform double entry and proofreading. For questions in the case report form, the data administrator will generate a question-answer form and send an inquiry to the researcher through the clinical monitor. The researcher should answer the question as soon as possible, and the data administrator will modify the data according to the researcher's answer. If necessary, a question answer form can be issued again.

### Monitoring

An independent Data and Safety Monitoring Board will be set up prior to the start of the study. The DSMB will review data after the first participant, and then after the recruitment of 25, 50, and 75% of participants to check the study progress and all adverse events.

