## Methods/Design

### Study objectives

In this study setting, the metabolic syndrome was defined as abdominal obesity, prediabetes (Impaired Glucose Tolerance), high cholesterol, and high blood pressure, not including diabetes. The aim of this study is to evaluate the effectiveness of Jinlida in delaying or inhibiting the development of diabetes mellitus in metabolic syndrome subjects with impaired glucose tolerance. We hypothesize that general lifestyle intervention + Jinlida granule is more effective than placebo + general lifestyle intervention in delaying or inhibiting the development of diabetes mellitus in metabolic syndrome subjects with impaired glucose tolerance. If successful, this work will provide clinical evidence for high-risk factors requiring intervention to prevent arteriosclerosis and inhibit the development of the cardiovascular pathology.

A total of 880 patients will be enrolled in this study over the course of 2 years. Recruitment takes place at an out-patient clinical institution. The principal investigators or investigators inform the patients (orally and in writing) about benefits and risks of participating in the study and of the clinical assessments and randomized allocation of treatment. Patients have to provide written consent before enrolling in the study. Patients may withdraw their consent to participate at any time without providing a reason. There is no financial compensation for the subjects. However, all clinical evaluations and study medication have no cost for the patients.

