### Setting and Participants

This study will be conducted at 22 Collaborative Research Centers in China. Recruitment will be by advertisement in local free papers and by posters displayed in 22 Collaborative Research Centers as well as we disseminate relevant recruitment information in the community. The recruitment began in August 2019, and it will be completed within 2 years. All the participants will receive oral and written information regarding the study by a doctor involved in this work.

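### The listed DSMB reviews are all triggered by recruitment and end at 75% enrolled, so most of the planned drug exposure falls after the last one

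*Protocol article*

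**What the plan says.** The Monitoring section sets up an independent board and gives its timetable: "The DSMB will review data after the first participant, and then after the recruitment of 25, 50, and 75% of participants". The stated purpose is "to check the study progress and all adverse events". No review is tied to calendar time, time on drug or number of events.

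On recruitment, Setting and Participants says "The recruitment began in August 2019, and it will be completed within 2 years", and Study objectives says "A total of 880 patients will be enrolled in this study over the course of 2 years".

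On duration, the sections do not agree:
- Treatment: "Treatment duration is at least 2 years". Study Procedure says the same.
- Intervention Cycles: "the intervention will last 24–48 months", followed by a statement that follow-up lasts 24 months.
- Sample Size Calculation: "The study period will last 4 years, including 2 years of medication treatment and 2 years of follow-up".

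Table 1 has adverse events assessed at every visit, including the column that runs to month 48. Blood and urine routine, liver and kidney function and ECG are done at months 6 and 12 and repeated later.

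**The concern.** The board's timetable follows the pace of enrolment, while the safety information builds up with time on drug. Recruitment is planned to end halfway through a 4-year study, and the last listed review comes before even that. Effects of cumulative exposure, differences between arms in withdrawal, and the cardiovascular and cerebrovascular events named in the Withdrawal Criteria would mostly appear later. The trial collects those later data, but the timetable as written brings none of them to the board. The Discussion itself warns that the long treatment period may harm compliance, and the listed checks of study progress stop at the same point.

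**Working it through.** **1. Does the plan's own design reproduce?** Inputs from Sample Size Calculation: 40% control incidence at 2 years, HR 0.75, α = 0.05 (two-sided under Statistical Analysis Method), power 80%, 1:1 allocation, 4-year study. The 2-year accrual comes from Study objectives.

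- Events (Schoenfeld): 4(1.960 + 0.842)² / (ln 0.75)² ≈ 380.
- Hazards per year: control λ₀ = −ln(0.6)/2 = 0.2554; Jinlida λ₁ = 0.75 × 0.2554 = 0.1916.
- Event probability with uniform accrual over 2 years and a common close at 4 years: 1 − (e^(−2λ) − e^(−4λ))/(2λ) = 0.530 and 0.434.
- Subjects per arm: 380 / (mean of 0.530 and 0.434) / 2 = 394.3, so 395 as stated.
- Events with 395 per arm: 209.4 and 171.3, against the stated 209:171.
- 10% allowance: 790/0.9 = 878, stated as 880.

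The sample size therefore fits 2-year uniform accrual with 24–48 months (mean 36) of follow-up. It does not settle how much of that follow-up is on drug.

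**2. When is the last listed review?** Under uniform accrual over 24 months, the 25, 50 and 75% triggers fall at months 6, 12 and 18. At month 18 there are 0.75 × 880 = 660 subjects with 0–18 months on drug, on average 9. More generally, whenever recruitment finishes within 24 months, the 75% point comes before month 24. Nobody can then have completed the 24-month minimum at any listed review.

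**3. How much exposure comes after it?** Ignoring exits, exposure at month 18 is 660 × 9 = 5,940 patient-months (495 person-years).

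If exposure stops at diabetes, a subject with planned time t contributes (1 − e^(−λt))/λ. Averaged over both arms and over t uniform on 0–1.5 years, this gives 0.673 years × 660 = 444 person-years. For the common close, averaging over t uniform on 2–4 years gives 2.170 years × 880 = 1,909 person-years.

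| Drug duration (uniform 24-month accrual) | Planned exposure, no exits | Share after last listed review | Same, if exposure stops at diabetes |
|---|---|---|---|
| 24–48 months, common close at month 48 | 880 × 36 = 31,680 patient-months | 81.25% | 76.7% (1 − 444/1,909) |
| 24 months each | 880 × 24 = 21,120 | 71.9% | 68.7% |
| 48 months each | 880 × 48 = 42,240 | 85.9% | 81.0% |

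Longer exposure is seen even less. With the common close, time beyond the first 12 months on drug amounts to 220 × 0.25 = 55 person-years at month 18, of 880 × 2 = 1,760 planned (3%).

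**4. Other accrual patterns.** With accrual still ending at month 24 and the common close, the share is 83.8% (80.3% with exits) if accrual accelerates and 87.5% (83.5%) if it is front-loaded.

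If accrual overruns, the review moves later. Take uniform accrual over 36 months and 24 months of drug each (assumed for illustration). The 75% point is month 27. The 73.3 subjects enrolled in the first 3 months have then completed 24 months, and the other 586.7 average 12 months. Exposure is 73.3 × 24 + 586.7 × 12 = 8,800 of 21,120 patient-months, so 58% comes after.

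An overrun is plausible. Current Status reports 65 consented from August 2019 to May 2020. An even pace of 880/24 = 36.7 a month would give about 330 in nine months.

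**The case against.** The strongest reply is that the Monitoring section is two sentences in a journal article. It lists review points without saying that they are the only ones. A board charter or the full protocol could hold a later schedule and provision for ad hoc meetings. That stands to this extent: a reader might infer that the board never reviews the later exposure, but the article shows only that no later review is listed. It does not dispose of the point, because the article gives a specific timetable with its purpose, and that timetable, followed as written, stops at 75% enrolled.

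Second, the exposure share depends on on-time accrual and on which duration statement is used. This also stands. A single figure of about four fifths describes one scenario, so a range is needed.

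Third, a reader might conclude that subjects are unprotected in the later years. The article does not support that. Adverse events are assessed to month 48, and the individual withdrawal and discontinuation rules apply throughout. These do not replace a review of accumulating data by arm, but they are monitoring.

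Finally, two complaints that might be added correct nothing in the text. The first-participant review is a harmless early check. Whether the board sees unblinded tables is not stated either way.

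**Conclusion.** The point holds as a poorly fixed rule: the listed reviews follow recruitment and end before recruitment does, in a trial whose treatment runs for years. With on-time uniform accrual the last listed review is at about month 18, and roughly 70–85% of planned drug exposure lies beyond it. The best single figure is 81% (77% if exposure stops at diabetes) under the accrual and close that reproduce the stated sample size, provided drug is taken throughout. It is 69–72% if each subject takes drug for only 24 months, as Sample Size Calculation can be read. If recruitment slips to 36 months and drug lasts 24 months each, it is about 58%. In every scenario examined more than half of the exposure follows the last listed review. None of these percentages is printed in the article, and they cannot be fixed more closely until Treatment, Study Procedure, Intervention Cycles and Sample Size Calculation are reconciled on duration.

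**What to change.** Keep the existing early reviews. Add safety reviews at calendar or exposure intervals, for example every 6 months, until the last subject ends treatment, covering adverse events, withdrawals and cardiovascular events. If a charter already provides later reviews, correct the Monitoring section to say so. Separately, reconcile the statements on treatment duration so that the end of board oversight can be defined.

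With on-time accrual, 6-monthly reviews after month 18 fall at months 24, 30, 36 and 42, with month 48 coinciding with the close. Under the common close, 880 × 6 = 5,280 of 31,680 patient-months remain at month 42, so the board would have seen 83% of planned exposure instead of 19%.

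The cost is a few more reports from a board that the plan already provides for. Reviews confined to safety spend no alpha, and the article states no efficacy stopping rule. Dose, endpoint and sample size are unchanged.
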